#### Befriending (control)

The control condition, Befriending, is specifically designed to be the control intervention for clinical trials of psychology-based or ‘talking’ therapies. It offers the same clinician contact and involves meeting and talking with the participant in a supportive, friendly, but non-directive manner. It has been manualised and its outcomes formally assessed to allow it to serve as a theoretically justified ‘placebo’ group. It has become the standard control group in therapy trials for mental health, as it matches for expectancy, acceptability, enjoyment and engagement, while delivering no specific benefit on most outcomes.^18^ It will be administered by the same clinicians (physiotherapists) at intervals and duration matching the BCT sessions.

To provide equal opportunities, participants in the Befriending (control) group will be offered access to the BCT intervention (initial and booster session) after they have completed their 24-week follow-up questionnaires.

### Adherence

Adherence to BCT home exercises will be assessed from baseline to primary time point (Week 12). The physiotherapist will provide participants in the BCT group with a 3-month calendar style diary at the initial treatment session and ask them to record if and when they complete their recommended (daily) BCT exercises. The physiotherapist will review the adherence diary with the participant at the Week-4 booster session to gauge adherence to the treatment intervention. They will also contact the participant at Week 8 and Week 12 and ask them to return the adherence diary for these time points. Alternatively, BCT participants may complete the adherence diary via MyCap.

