**Ethics and dissemination:**

The study has been approved by The Austin Health Human Research Ethics Committee (HREC/84335/Austin-2022) and the New Zealand Central Health and Disability Ethics Committee (2022 FULL 12324). Findings will be reported to trial participants and consumers; presented at local, national and international conferences; and disseminated by a peer-reviewed scientific journal.

STRENGTHS AND LIMITATIONS OF THIS STUDYThe study has a large sample, and an international, multicentre design.The study uses a control arm matching the intervention for therapist time, and delivered by the same therapist.The study is only blinded to assessor; participant and therapist blinding is not possible.

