### Blinding

The physiotherapists will deliver the intervention to participants in an unblinded manner. The research assistant (RA), who will be administering the outcome measures, as well as the statisticians involved in data analysis, will be blinded to treatment allocation while the trial is active. After randomisation, participants will be asked not to reveal their group allocation to the RA. Given many of the outcome measures will be administered electronically (via REDCap), this will also assist RA blinding.

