Box 2Trial schematicClinical assessment (neurologist)Functional seizures diagnosis confirmed by epileptologist.Participant informed of trial.Informed consent obtained OR obtain consent for study staff to follow-up and discuss.PrescreeningEligibility confirmed using prescreening questionnaire.Informed consent (if not completed by referring clinician).Baseline study questionnaires completed: Demographics, The Assessment of Quality of Life Eight Dimension (AQoL-8D), Generalised Anxiety Disorder Assessment (GAD-7), Patient Health Questionnaire, 9-item (PHQ-9), Multiscale Dissociation Inventory (MDI), Nijmegen, Toronto Alexithymia Scale, Resource Use Questionnaire (RUQ), Seizure triggers and control, Seizure quality, Work and Social Adjustment Scale (WSAS).Medical record data extracted.RandomisationPhysiotherapist contacts participant to inform them of their group allocation and schedule first session.Initial treatment session (Breathing Control Training/Befriending): baseline60 min, one-on-one session with physiotherapist, conducted at clinical care site (or Telehealth if required).Seizure frequency and adherence diary provided.Booster treatment session (Breathing Control Training/Befriending): week 430 min, one-on-one session with physiotherapist, conducted at clinical care site (or Telehealth if required).Adverse events, seizure frequency and adherence diary reviewed by physiotherapist.Research assistant (blinded) sends self-report questionnaires to participant via Research Electronic Data Capture (REDCap): *AQoL-8D, Acceptability, GAD-7, PHQ-9, MDI, Nijmegen, Seizure quality, WSAS.*Primary endpoint: week 12Research assistant (blinded) sends participant self-report questionnaires via REDCap: *AQoL-8D, Childhood Experience of Care and Abuse Questionnaire, GAD-7, PHQ-9, MDI, Nijmegen, RUQ, Seizure triggers and control, Seizure quality, WSAS.*Adverse events and medication status reviewed by research assistant.For eligible and willing participants, invited to complete Life Events and Difficulties Schedule.Follow-up: week 24Research assistant (blinded) sends participant self-report questionnaires via REDCap: *AQoL-8D, GAD-7, PHQ-9, MDI, Nijmegen, RUQ, Seizure quality, WSAS.*Participants randomised into the Befriending (control group) offered access to the BCT intervention.Observational follow-up: week 52, week 78 and week 104 (optional)Participants sent self-report questionnaires via REDCap: *AQoL-8D, GAD-7, PHQ-9, MDI, Nijmegen, RUQ, WSAS, seizure frequency (for previous 4*

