##### Patient Health Questionnaire, 9-item

A 9-item self-report questionnaire used to aid in the diagnosis of depression, as well as monitoring the severity of symptoms. Items correspond to the DSM-IV diagnostic criteria for major depressive disorder. Responders are asked to rate how much they have been bothered by each item based on the previous 2 weeks via a 3-point Likert scale (0=not at all; 3=nearly every day). An overall severity score is obtained by totaling the 9 items (mild depression: 5–9; moderate depression: 10–14; moderately severe depression: 15–19; severe depression: 20–27). The Patient Health Questionnaire, 9-item is estimated to take 1–2 min to complete.^34^

A tailored RUQ developed by health economists from Monash University (Melbourne, Australia) will ascertain participants’ utilisation of healthcare resources and lost productivity in the previous 3 months. This includes items which explore medication use, emergency department presentations, ambulance assistance, hospitalisations and clinician visits. The RUQ is expected to take 5–8 mins to complete.

Participants randomised into the BCT group will be provided with a second diary to record if and when they complete their BCT home exercises up until primary endpoint (Week 12). This diary will also be available to complete on MyCap. If the latter, participants will receive a daily notification on their smartphone/tablet device asking them ‘did you complete your BCT homework yesterday?’ (yes/no).

Participants completing pen and paper diaries (or electronically on a computer) will be reminded by the physiotherapist to return the first month’s diary at the ‘booster’ session for review. Thereafter, at the end of each monthly cycle until Week 24, participants will be contacted by study staff (emailed/texted) and asked to return their seizure diary (via email/post as they prefer). If participants do not respond to the email/text, they will be telephoned by study staff within 5 days to assist gathering this data. A copy of the diary will be uploaded into REDCap and FS frequency for the preceding 4 weeks calculated.

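### BCT-only physiotherapist contacts at Weeks 8 and 12, and a Week 4 review of outcomes by the unblinded physiotherapist, do not fit the article's statements on matching and blinding (minor)

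*Protocol article*

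**What the plan says.** **Contact.** The strengths and limitations list after the abstract says: "The study uses a control arm matching the intervention for therapist time, and delivered by the same therapist". The Befriending (control) section says of the comparator: "It offers the same clinician contact and involves meeting and talking with the participant". That section also says the Befriending sessions follow the spacing and length of the BCT sessions, and Table 2 gives 60 and 30 minutes.

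The Adherence section then describes what happens around the BCT exercise diary. At the booster session, "The physiotherapist will review the adherence diary with the participant at the Week-4 booster session to gauge adherence to the treatment intervention". The next sentence carries on with the same physiotherapists: "They will also contact the participant at Week 8 and Week 12 and ask them to return the adherence diary for these time points". The Measures section confirms that the diary belongs to one arm: "Participants randomised into the BCT group will be provided with a second diary to record if and when they complete their BCT home exercises". BCT participants may use the MyCap app for it instead, in which case "participants will receive a daily notification on their smartphone/tablet device asking them" whether they did the previous day's homework.

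**Blinding.** The Blinding section states that the physiotherapists are unblinded and that "The research assistant (RA), who will be administering the outcome measures, as well as the statisticians involved in data analysis, will be blinded" to allocation while the trial is active. Box 2 lists this under the Week 4 booster session: "Adverse events, seizure frequency and adherence diary reviewed by physiotherapist". In the same box the blinded research assistant sends the Week 4 and Week 12 questionnaires, and the research assistant reviews adverse events at Week 12.

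**The concern.** Befriending was chosen so that therapist attention, expectancy and engagement would be alike in the two arms, leaving the breathing training as the difference. Two further contacts from the treating therapist in one arm only are a departure from that aim. The first of them comes just as the four weeks that decide the primary outcome begin. If such contact had any effect of its own, the comparison would credit it to BCT.

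The second issue is separate. Adverse events are a named secondary outcome, reviewed at Weeks 4, 12 and 24. At Week 4, the review closest to treatment, the person going over them with the participant knows the allocation and delivered the treatment. Seizure frequency is reviewed in the same session. Week 4 remission may also enter the primary model, which includes visit and visit-by-group terms.

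**Working it through.** This is mainly a comparison of statements, with one count and one illustration.

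**1. Scheduled physiotherapist contacts to Week 12** (Intervention and comparator; Adherence; Table 2)

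| | BCT | Befriending |
|---|---|---|
| Initial session | 60 min | 60 min |
| Booster, Week 4 | 30 min | 30 min |
| Diary contact, Week 8 | yes, length not given | none described |
| Diary contact, Week 12 | yes, length not given | none described |
| Number of contacts | 2 + 2 = 4 | 2 + 0 = 2 |
| Session time | 60 + 30 = 90 min | 60 + 30 = 90 min |

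Session time is matched. The number of clinician contacts is not. Both arms are also contacted monthly about the seizure diary, but the Measures section assigns that to study staff, so it does not replace the missing physiotherapist contact in Befriending.

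**2. Position relative to the primary window.** Remission at Week 12 means no seizures in the preceding 4 weeks, so the window runs from the end of Week 8 to the end of Week 12. The Week 8 contact opens it and could act on seizures within it. The Week 12 contact closes it and cannot change seizures already past.

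**3. Who handles which outcome**

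- Week 4 questionnaires: sent by the blinded research assistant (Box 2).
- Week 4 adverse events and seizure frequency: reviewed by the unblinded physiotherapist (Box 2). Paper and computer diaries for the first month are returned at that session (Measures).
- Week 12 questionnaires and adverse events: research assistant (Box 2).
- Week 12 primary outcome: recorded by the participant (Box 1). After the first month, diaries are requested by study staff (Measures).
- Week 24 adverse events: scheduled in Table 3, but Box 2 names no reviewer.

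The documented conflict with the Blinding section is therefore the Week 4 adverse event and seizure-frequency review, and nothing beyond it.

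**4. Illustration of size, by assumption only.** The plan's own sample size comes first. With 20% v 40%, two-sided 5% and 80% power, the pooled-variance formula gives

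n = [1.96·√(2·0.30·0.70) + 0.842·√(0.20·0.80 + 0.40·0.60)]² / 0.20² ≈ 81.2, so 82 per arm; 82 / 0.75 = 109.3, so 110 per arm and 220 in total.

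This matches the protocol. Now suppose that BCT has no specific effect and that the extra contact alone adds b to a 20% remission rate. The chance of a significant result favouring BCT with 82 evaluable per arm is

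Φ{ [b − 1.96·√(2·p̄(1−p̄)/82)] / √[(0.16 + p(1−p))/82] }, where p = 0.20 + b and p̄ = 0.20 + b/2.

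- b = 0.02: about 5%
- b = 0.05: about 12%
- b = 0.10: about 31%

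With b = 0 the figure is 2.5% in that direction. The documents give no basis for any of these values of b, and two requests to return a diary may well have an effect near zero.

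**The case against.** The case on the other side is substantial, and most of it stands.

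- What the Befriending section spells out as matched is session interval and duration, and those are matched. The extra contacts are described only as asking for a diary back. No length or therapeutic content is given, so four against two does not mean twice the treatment.
- MyCap is offered as an alternative to the diary that is chased, so the contacts may not apply to those participants.
- A reader might add the app's homework prompts, up to 12 × 7 = 84 by Week 12 against none, as further unmatched attention. The documents do not support that reading well. Recording home practice in a diary is part of BCT as the article describes it, so the prompts are arguably part of the package being tested. Seizure-diary reminders go to both arms, weekly, or daily through the app.
- A reader might also infer that adherence contacts change how completely the seizure diary is kept. Nothing in the article shows this, and that diary has its own reminders and telephone follow-up in both arms.
- At Week 4 the physiotherapist is said to review the data, not to rate them. The participant writes the seizure record, and the frequency is calculated from the uploaded diary. The Participant safety section has the site principal investigator or delegate judge severity, seriousness, relatedness and expectedness, with all events going to an independent monitoring board. The physiotherapist also manages symptoms in the BCT session, so some therapist knowledge of events cannot be avoided.

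These arguments limit the point without removing it. The wording on clinician contact is not confined to sessions, and the adherence contacts are assigned to the physiotherapist in one arm only. The article admits that therapists are unblinded, but not that they take part in reviewing outcomes.

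**Conclusion.** The point holds in a limited form and is minor. (a) Physiotherapist contact is unequal by two scheduled contacts, at Weeks 8 and 12, in BCT only. Only the first could bear on seizures in the primary window. The size of any effect is unknown and may be negligible. (b) At Week 4, one of three adverse event reviews and the seizure-frequency review involve an unblinded therapist, contrary to the Blinding section.

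A reader might conclude that the trial's assessment as a whole is not blinded as claimed. The article does not support that: the Week 12 primary outcome is participant-recorded, and the Week 12 questionnaires and adverse events go through the research assistant. The larger threat to the primary outcome is self-report by unblinded participants, which the article acknowledges. Neither point changes the sample size.

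This assumes that the Adherence section is complete about who makes the Week 8 and Week 12 contacts, and that the full protocol describes no matching contact for Befriending.

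**What to change.** - **Contact.** Send the Week 8 and Week 12 adherence-diary requests by automated REDCap or MyCap message, or by the email and text route that study staff already use for seizure diaries. Whoever sends them should not be the blinded research assistant, since handling a BCT-only diary would reveal the allocation. Alternatively, give Befriending participants the same brief physiotherapist contact at the same weeks.
- **Week 4 data.** Have the blinded research assistant or a REDCap form collect adverse events and seizure counts in both arms, as the research assistant already does for adverse events at Week 12. The physiotherapist's handling of symptoms within sessions is unaffected.
- **If the procedures stay.** Qualify the strengths statement and the Befriending section so that they claim matched session time only, and state in the Blinding section that the Week 4 adverse event and seizure-frequency review is done by the unblinded physiotherapist.

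The cost is a small change to the message and form schedule, and possibly a slightly lower return of adherence diaries. The alternative costs two short contacts per Befriending participant. No new staff are needed.

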### Concomitant care

The BCT/Befriending will be used in addition to the participants’ standard care, that is, they will continue their ‘treatment as usual’ (TAU) while they are enrolled in the trial. Standard care can vary widely in this patient group, particularly when newly diagnosed with FS. For example, some patients may be taking (or withdrawing from) antiseizure medications and/or other pharmacotherapies; see a neuropsychiatrist, psychologist or other allied health professionals; whereas others may not be receiving treatment. There are no restrictions on what standard care can/cannot entail while they participate in the trial; however, if they are engaging in therapies which focus on specific breathing techniques (eg, box breathing, Buteyko method), they will be excluded from the trial.

Study staff will record all concomitant therapies at baseline and follow-up appointments, assisted by a tailored, self-reported Resource Use Questionnaire (RUQ), and for consenting Australian participants, accessing Medicare Benefits Schedule (MBS) and Pharmaceutical Benefits Scheme (PBS) data from Services Australia. For consenting Australian participants living in Victoria, health service use data (hospital admissions, emergency department presentations and community healthcare services) will also be retrieved from The Centre for Victorian Data Linkage (CVDL). Collectively, these data will capture what each participant’s TAU entails, as well as changes to TAU throughout the trial.

### Participants eligibility

Eligibility criteria are outlined in table 1.

**Table 1 T1:** Inclusion and exclusion criteria

Inclusion criteria	Exclusion criteria
≥16 years of age	Comorbid epilepsy
Able to provide written, informed consent	Currently engaging in other breathing therapy treatments/clinical trials
Diagnosis of FS confirmed by an epileptologist based on at least one typical event captured on video EEG	
Self-reported FS frequency of at least two per month in the preceding 4 weeks	
English sufficient to complete questionnaires and understand the treatment intervention	

EEG, electroencephalography; FS, functional seizures.

### Participant safety

#### Risk management and safety

From our own pilot data, and randomised-controlled trials of breathing exercises for asthma, BCT’s excellent safety and tolerability profile is evident.^19 20^ Nonetheless, AEs will be reviewed and monitored throughout the trial to further explore BCT’s safety profile in FS specifically. As per the trial, physiotherapists (informed by their own clinical practice) expected side effects of BCT to include transient lightheadedness, breathlessness and/or feelings of panic in some individuals. These symptoms can be managed by the respiratory physiotherapist in the BCT session.

AEs will be defined as ‘any untoward medical occurrence in a…clinical trial participant administered a medicinal product and that does not necessarily have a causal relationship with this treatment’,^21^ and will include:

Pre-existing conditions not reported at baseline.Worsening of a pre-existing condition.Diagnosis of a new condition/disease.New symptoms.Abnormal laboratory findings which are identified after randomisation into the trial

Serious AEs (SAEs) will be defined as ‘any adverse event that results in death, is life-threatening, requires hospitalisation or prolongation of existing hospitalisation, results in persistent or significant disability or incapacity, or is a congenital anomaly or birth defect’.^21^ In this trial, if a participant presents to emergency due to a FS, it will not be considered an SAE (as this can be a common occurrence in FS). However, details of the attendance will be reviewed and recorded by study staff, and also captured on the RUQ (self-reported by the participant).

The participant will be asked about the presence of adverse events at Week 4, 12 and 24, and details recorded in the corresponding Research Electronic Data Capture (REDCap) instrument. Severity, seriousness, relatedness (causality) and expectedness of AEs to the intervention will be assessed by the site principal investigator (PI) or delegate. All AEs/SAEs will be reported to an independent Data Safety Monitoring Board comprising an epileptologist, psychiatrist, physiotherapist and statistician for review. No interim analyses are planned.

After completion of the Childhood Experience of Care and Abuse Questionnaire (CECA-Q; self-report) at Week 12, participants will be encouraged to contact their study doctor if they have any concerns or become distressed. The contact details for their study doctor will be reiterated at the start of the questionnaire. For participants who disclose experiencing sexual abuse in childhood, a follow-up question will appear in REDCap asking if they would like the abuse to be reported to the authorities. Participants may select ‘Yes – I would like this to be reported. I understand that one of the study doctors will contact me to discuss the options available for reporting, including support services I can contact’ or ‘No – I do not give permission for this to be reported’. If they select ‘Yes’, one of the study doctors will contact the participant to discuss reporting procedures in further detail and address any of the participants queries/concerns. Contact details for support services will also be provided, if desired.

For participants who are eligible (FS onset within the last 2 years) and willing to undertake the Life Events and Difficulties Schedule (LEDS) at Week 12, there is a theoretical risk of distress as these assessments will explore potentially traumatic events from the participant’s past. In the event a participant should find these assessments distressing and which cannot be managed by the interviewer, they will be referred to neuropsychiatry clinics at their hospitals, free public clinics with specialist expertise in the diagnosis and management of FS and their complications; or escorted to the hospital’s emergency department if more urgent care is required.

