Box 1OutcomesPrimarySeizure remission, defined as seizure frequency of zero in the preceding 4 weeks (recorded by the participant in a seizure frequency diary), measured at Week 12 (12 weeks post the initial treatment session).SecondaryChanges in hyperventilation from baseline, measured by the Nijmegen scale of hyperventilation provided at baseline, Week 4, Week 12 and Week 24.Changes in healthcare utilisation from baseline, measured via a tailored resource use questionnaire provided at baseline, Week 12 and Week 24, as well as changes in health service use ascertained from Services Australia and CVDL data (Services Australia and CVDL data for consenting participants only).Changes in quality of life from baseline, measured by the Assessment of Quality of Life Eight Dimension provided at baseline, Week 4, Week 12 and Week 24.Changes in depression and anxiety symptoms from baseline, measured by the 9-item Patient Health Questionnaire and Generalised Anxiety Disorder Assessment respectively, provided at baseline, Week 4, Week 12 and Week 24.Changes in occupational and social functioning from baseline, measured by the Work and Social Adjustment Scale provided at baseline, Week 4, Week 12 and Week 24.Acceptability of BCT captured by a tailored self-report questionnaire provided after attending the Week 4 ‘booster’ session.Safety of BCT assessed by the occurrence of adverse events reviewed at Week 4, Week 12 and Week 24.tcCO_2_ levels (mm Hg; a marker of hyperventilation) preceding or during seizures, BPAT score (at baseline) and/or Nijmegen score (at baseline), to predict response to treatment.ExploratoryThe presence of significant life events in childhood and adolescence (≤16 years of age), and 12 months preceding the onset of their FS, assessed via the Childhood Experience of Care and Abuse Questionnaire and the LEDS*, respectively, to gauge moderators of treatment response.The MDI and Toronto Alexithymia Scale provided at baseline will be assessed if predictors of treatment response. MDI scores at Week 4, Week 12 and Week 24 will be assessed if they correlate with treatment response.*Note, the LEDS is optional, and only relevant to participants whose FS have started within the last 2 years.BCT, breathing control training; BPAT, Brompton Breathing Pattern Assessment Tool; CVDL, Centre for Victorian Data Linkage; FS, functional seizures; LEDS, Life Events and Difficulties Schedule; MDI, Multiscale Dissociation Inventory; tcCO_2_, transcutaneous carbon dioxide.

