#### Measures

In addition, the following measures and standardised clinical questionnaires will be used in the trial (see table 3, box 2, for scheduling). All self-reported questionnaires will be completed via REDCap.

**Table 3 T3:** Participant timeline

Assessment/ procedure	Clinical assessment (neurologist)*	Prescreening	Initial session with physio (baseline)	‘Booster’ session (Week 4) with physio	Follow-up (Week 12†)	Follow-up (Week 24)	Week 52, 78 and 104 observational follow-up (optional)
Video EEG	x						
tcCO_2_ monitoring	x						
FS semiology and chronicity	x						
Medical hx (inc. family hx and psychiatric hx)	x						
Informed consent		x					
Confirm eligibility		x					
BCT/Befriending intervention			60 mins X	30 mins X			
Seizure frequency diary		For preceding 4 weeks	Recorded by the participant throughout the 24-week trial period (automated reminders sent weekly via text/email, or daily via MyCap)				For preceding 4 weeks
Seizure control and triggers		x			x		
Seizure quality		x		x	x		
Demographics		x					
AQoL-8D		x		x	x	x	x
Nijmegen scale		x		x	x	x	x
GAD-7		x		x	x	x	x
PHQ-9		x		x	x	x	x
WSAS		x		x	x	x	x
TAS		x					
MDI		x		x	x	x	x
RUQ		x			x	x	x
Adverse events				x	x	x	
Acceptability questionnaire				x			
LEDS (optional)					x		
CECA-Q					x		

* Standard care

† Primary endpoint

AQoL-8D, The Assessment of Quality of Life 8 Dimension; BCT, Breathing Control Training; CECA-Q, Childhood Experience of Care and Abuse Questionnaire; EEG, electroencephalogram; FS, functional seizures; GAD-7, Generalised Anxiety Disorder Assessment; Hx, history; LEDS, Life Events and Difficulties Schedule; MDI, Multiscale Dissociation Inventory; PHQ-9, Patient Health Questionnaire, 9-item; RUQ, Resource Use Questionnaire; TAS, Toronto Alexithymia Scale; WSAS, Work and Social Adjustment Scale.

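### No adverse-event enquiry is scheduled at the 60-minute first session, so brief symptoms that BCT is expected to cause there may be under-recorded (cheap improvement, low priority)

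*Protocol article*

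**What the plan says.** The text under Risk management and safety sets the enquiry points: "The participant will be asked about the presence of adverse events at Week 4, 12 and 24". Box 1 defines the secondary safety outcome by the same times: "Safety of BCT assessed by the occurrence of adverse events reviewed at Week 4, Week 12 and Week 24". In Table 3 the adverse-events row is marked at the Week 4 booster, Week 12 and Week 24; it is blank under the column headed "Initial session with physio (baseline".

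Box 2 lists only the session itself and the diaries at the initial visit. Its first adverse-event item is at the booster, "Adverse events, seizure frequency and adherence diary reviewed by physiotherapist", and the next is at Week 12, "Adverse events and medication status reviewed by research assistant".

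On what harms to expect, the safety section reports that the physiotherapists "expected side effects of BCT to include transient lightheadedness, breathlessness and/or feelings of panic in some individuals", and adds: "These symptoms can be managed by the respiratory physiotherapist in the BCT session". The same section counts new symptoms, and worsening of a condition already present, as adverse events. It also says in general terms that adverse events are monitored for the whole trial, with the aim of learning more about BCT's safety in functional seizures.

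**The concern.** The harms that the protocol itself predicts are brief and are placed in the treatment session. The first session is the longest and is the participant's first exposure to BCT, but the first scheduled question about harms comes about four weeks later. A short spell of lightheadedness that passes with the physiotherapist's help is easily forgotten, or not thought worth mentioning, by then.

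Safety is a declared secondary outcome. The expected symptoms belong to BCT and not to Befriending, so any loss would fall mainly on the BCT arm and make it look somewhat more benign than it is. The existing evidence in this population is thin: the pilot described in the Introduction recruited 18, followed up 10 and reported no adverse events.

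**Working it through.** The plan gives no figure on this point, so the check is a comparison of the places that bear on it.

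1. **When is the first enquiry?** The safety text, Box 1, Table 3 and Box 2 all give Week 4. Box 2 does not list an adverse-event item at Week 24, but that does not affect the first enquiry. Because the sources agree, the absence at the initial session is a feature of the stated schedule and not a slip in one table.

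2. **Would the expected symptoms count as adverse events?** Yes, if new or worse than before, under the section's own list.

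3. **Where are they expected?** In the BCT session, where the physiotherapist is to manage them. The Breathing control training section gives 60 minutes for the first session and 30 minutes for the second, 4 weeks later.

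4. **Is there a stated recording step at the first session?** None is found. The form completed at the end of each session (Training and fidelity) is a fidelity checklist and is not described as a record of harms.

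5. **What later routes could recover a first-session event?**
   - *Attends the booster:* asked at Week 4 by the physiotherapist, who will normally also have run the first session. The acceptability questionnaire has a free-text field, but it too comes only then: "Acceptability of BCT captured by a tailored self-report questionnaire provided after attending the Week 4" booster session.
   - *Misses the booster but stays in the trial:* still asked at Weeks 12 and 24.
   - *Withdraws from the trial before Week 4:* offered an exit interview that covers adverse events but may be declined (Participant safety and withdrawal).

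The gap is therefore one of recall for most participants. It becomes a possible absence of any enquiry only for those who withdraw before Week 4 and decline the interview. The document gives neither the frequency of in-session symptoms nor the timing of withdrawals, so no rate of under-recording can be derived.

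**The case against.** The best defence has three parts. First, the schedule is conventional: each enquiry covers the interval since the last contact, so Week 4 covers the first session, and the person asking will usually have been in the room. Second, the statement that adverse events are monitored throughout the trial may already oblige the physiotherapist to record what is witnessed, with the procedure set out in a fuller document. Third, the events are mild and expected.

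Much of this stands. It is why the point is only that events may be under-recorded, and why its priority is low. What remains is that the article fixes the enquiry times and ties the safety outcome to them. The general monitoring statement adds no time point, and no recording step accompanies the statement that symptoms are managed in the session.

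A reader might infer more, in three ways that the document does not support:

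- **That first-session events go unrecorded.** The Week 4 review and the general monitoring statement both argue against this.
- **That anyone who misses the booster is asked only at an exit interview.** Missing a session is not among the listed reasons for withdrawal, and those who stay in the trial are asked at Weeks 12 and 24.
- **That the 25% drop-out allowance measures the group at risk** (0.25 × 110 = 27.5 per arm). That would require all drop-out to be formal withdrawal before Week 4. The timing is not given, and the same section cites attrition under 10% for BCT.

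**Conclusion.** The point holds in a limited form. The stated schedule fits the protocol's own description of expected harms poorly, because it sets no enquiry at the session where those harms are first expected. Brief first-session symptoms may be under-recorded, chiefly in the BCT arm, with the greatest risk among participants who withdraw before Week 4.

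The size cannot be computed from the document. The effect is confined to the completeness of the secondary safety outcome; the primary outcome is unaffected.

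The conclusion assumes that no procedure outside the article already requires in-session events to be recorded in both arms. If one does, marking Table 3 and Box 1 accordingly would settle the matter. This is a cheap improvement of low priority.

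**What to change.** Add one open question, worded identically in both arms, to the checklist that the physiotherapist completes after the initial session: was there any new symptom, or worsening of a usual symptom, during this session? Do not list BCT-specific symptoms, which would prompt one arm more than the other. Enter positive answers with an onset date in the existing REDCap adverse-event instrument. Mark the initial session in the adverse-events row of Table 3 and in Box 1. Report these events by arm, separately from those reported at Weeks 4, 12 and 24, so that the existing counts keep their meaning.

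**Cost.** At most 220 extra answers (220 participants × 1 session) on a form already in use, an onset-date field if REDCap lacks one, and two small text changes. No new visit or staff are needed.

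**Downsides.** The recorder is unblinded, as at the existing Week 4 review. Breathlessness and lightheadedness also occur as pre-seizure symptoms (Seizure Control and Triggers Questionnaire), so some usual symptoms may be logged; asking about new or worsened symptoms limits this but does not remove it. BCT's event rate may look slightly less favourable. Symptoms during home practice would still rely on the Week 4 enquiry.
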